## Abstract

**Introduction:**

The rising prevalence of autism spectrum disorder (ASD) among children poses significant challenges for healthcare services. Research has underscored the crucial role of children’s involvement in their healthcare. However, due to the intricate nature of ASD, marked by communication and social interaction differences, healthcare providers face challenges in tailoring their services to accommodate these children. This project aims to explore the impact of two distinct needs assessment models on children’s participation in the needs assessment process.

**Methods and analysis:**

We will conduct a prospective observational study comparing responses from children subjected to two different needs assessment procedures: survey-based and meeting-based. Supplementary data will be collected from the children’s parents/guardians and healthcare professionals. Data collection methods will include questionnaires, interviews and document analysis of individual habilitation plans. We aim to recruit 120 children aged 7–17 diagnosed with ASD but without intellectual disability, with 60 undergoing the survey-based needs assessment and 60 undergoing the meeting-based assessment. The primary outcome measure will be the perception of participation in the needs assessment procedure. Secondary outcomes will include the children’s quality of life and mental health; the parents’ knowledge of their child’s strengths, abilities and special needs; and the parents’ perception of the quality of collaboration with the healthcare team.

**Ethics and dissemination:**

The study received ethics approval from the Swedish Ethical Review Authority on 4 March 2024 (reference number 2024-00227-01). All children and their caregivers will receive both verbal and written information about the study before being asked to provide written informed consent to participate. The findings will be disseminated through publication in peer-reviewed journals and presentation at conferences. Additionally, a popular science report summarising the data and its interpretation will be published.

**Trial registration number:**

NCT06381856.

STRENGTHS AND LIMITATIONS OF THIS STUDYUser involvement will be a key aspect.The study will contribute to our understanding of how to enhance the participation of autistic children and adolescents in their healthcare.Mixed methods will be used, analysing quantitative and qualitative data from the participating children, parents/guardians and healthcare professionals.This will be a non-randomised observational study with limited possibility for causal inferences.The study will focus on children with autism spectrum disorder, so the findings may not be generalisable to children with other disabilities.

## Introduction

 Autism spectrum disorder (ASD) presents as a multifaceted neuropsychiatric developmental condition characterised by challenges in social communication along with restricted, repetitive and stereotyped behaviours and interests.^1^ The prevalence of ASD in children varies across studies, with a global estimate of approximately 1%.^2^ Notably, Sweden exhibits a higher prevalence, around 1.6%, ranking among the highest worldwide when assessed using standardised diagnostic criteria such as International Classification of Diseases, Tenth Revision; Diagnostic and Statistical Manual of Mental Disorders, Fourth Edition; or Autism Diagnostic Observation Schedule.^2 3^ Moreover, there has been a notable surge in autism diagnoses globally over recent decades,^4^ with Sweden experiencing a particularly substantial increase.^5^

Sweden has complementary healthcare for all children, and this increase in ASD diagnoses among children poses a significant challenge to the healthcare providers tasked with meeting these children’s specialised needs, particularly those in Child and Youth Habilitation Centres (CYHCs). Central to this challenge is ensuring that CYHCs can effectively address these needs within a reasonable timeframe.

Research has underscored the importance of actively involving children as participants in their habilitation process.^6^ Participation entails two key aspects: first, the child’s attendance, colloquially referred to as ‘being there’, and second, their active engagement and involvement while ‘being there’.^7^ However, a notable gap exists in our understanding of the optimal level of participation for children, especially concerning the mapping of needs and prioritisation of interventions. This gap is particularly pronounced for children with autism, who often deal with challenges in social interaction and communication while also exhibiting repetitive behaviours and narrow interests. These traits can impede the child’s ability to comprehend and engage with topics outside their own interests, complicating their participation in various activities. Consequently, CYHCs are continually refining their processes to enhance these children’s functioning and overall well-being. The initial reception at the CYHC plays a crucial role in this process. However, the degree of a child’s participation in this initial phase remains a subject of inquiry, especially concerning needs assessment and intervention prioritisation.

Enhanced participation of children is also linked to improved mental health outcomes^8^ and quality of life (QoL),^9^ which is particularly significant given the elevated prevalence of co-occurring mental health issues among individuals with autism.^10^,^12^ Thus, it is pertinent to explore the relationship between participation and mental health outcomes for children and adolescents with autism, especially within the context of the initial reception process at CYHCs. While existing research on the impact of autistic children’s participation on mental health is limited, studies involving children with other disabilities suggest a positive correlation.^13^ Thus, there is a need to shed light on the intricate interplay between participation, mental health outcomes and the efficacy of innovative assessment models in meeting the diverse needs of children and adolescents with autism.

### The present study

Given the arguments mentioned above, the present study aims to address these gaps by examining the relationship between participation, mental health outcomes and the efficacy of a new needs assessment model at a CYHC in central Sweden. This model emphasises increased child involvement in needs assessment and goal-setting processes, which could result in the development of more personalised and meaningful intervention plans for the children.

The current survey-based needs assessment model offers a significant advantage in shorter waiting times. However, it comes with a drawback: children with multiple needs receive several interventions simultaneously. This results in a slower and more fragmented habilitation process, often leading to lower participation evaluations in patient surveys. In response to these challenges, the CYHC is implementing a novel needs assessment procedure tailored for the intake of children diagnosed with ASD. The primary purpose of this new assessment model is to enhance the child’s participation in both assessment and goal-setting processes. By doing so, it aims to more effectively identify and prioritise the child’s needs, facilitating a prompt and targeted intervention. Following this initial intervention, additional interventions can be offered to address less prioritised needs, ensuring a comprehensive approach to the child’s care.

In this updated approach, the child and their parent are invited to an initial personal meeting where they receive essential information about the CYHC, engage in discussions about the child’s diagnosis and conduct a preliminary needs assessment. Following this, the child and parent participate in four additional personal meetings to delve deeper into the child’s needs and to establish clear goals that are meaningful to the child.

Because the child’s participation in the needs assessment is an important component of the new reception model, the abovementioned previous research suggests potential effects on the child’s mental health. It is therefore of interest to study the connection between level of participation and mental health, both in the child and in the parents. Another question that is raised in the project is whether by having the parent present at the meeting, the new needs assessment model will lead to the parent changing their view on their child’s ability to act. If the parent perceives their child as competent in the meeting with professionals, this may have a beneficial effect on the child’s self-confidence, which in turn has significance for the child’s participation and mental health.

The interventions at the CYHC are tailored to each child’s specific needs through collaborative intervention planning involving both families and healthcare professionals. Central to this process is the acknowledgement of the child’s perspective and ensuring their voice is heard. The study seeks to explore whether increased child participation correlates with the formulation of more individual-specific goals in the children’s individual habilitation plans (IHPs). These plans function not only as documents but also as dynamic processes, providing guidance to professionals and families in effectively addressing the child’s requirements. In summary, this research endeavours to shed light on the intricate interplay between participation, mental health outcomes and the efficacy of innovative assessment models in meeting the needs of children and adolescents with autism.

### Aim

The primary aim is to investigate the effect of two needs assessment models on children’s participation in the needs assessment process from the child’s, parent’s and professional’s perspective. The secondary aim is to investigate the association of perceived participation with mental health, QoL and formulation of goals in the child’s IHP.

## Methods and analysis

### Study design

The study is a prospective observational study comparing responses from children and parents who underwent a survey-based assessment procedure to responses from those who instead had a meeting-based assessment procedure.

### Participants and sample size

To be eligible for participation in the study, a child or adolescent must be aged 7–17 with a diagnosis of ASD without intellectual disability. No other exclusion criteria will be applied. A power analysis was conducted based on results obtained from pilot testing of items in the Child Involvement Questionnaire (the primary outcome). This analysis determined that 60 children would be required in each group, totalling 120 children, to detect a moderate effect size difference between groups (Cohen’s d=0.5) with 80% power and a 5% alpha level. Since the main focus of the study is on children’s participation, no power calculation was conducted for the number of parents or staff involved. Given an expected intake of eligible children ranging from 300 to 400 per year at the CYHC and assuming a response rate of about 30% (based on experience from previous studies at the CYHC), the data collection period is estimated to be approximately 1 year.

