### Data analysis plan

Descriptive statistics will be used to summarise the sociodemographic characteristics of the children and their families. The questionnaires will be analysed using inferential statistical analysis such as t-test and analysis of variance, whereas associations between variables will be analysed by correlation and multiple regression. Multiple imputation will be used to handle missing data. The individual interviews will be transcribed verbatim and then analysed with inductive content analysis as described by Graneheim and Lundman.^20^ Document analysis of excerpts of the children’s IHP’s will be performed with quantitative content analysis according to Krippendorf^21^ and qualitative content analysis as described by Graneheim and Lundman,^20^ with a focus on descriptions of formulated goals. Trial findings will be reported according to CONSORT 2010 guidelines.^22^ The SPIRIT reporting was used for this submission.^23^

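### Sixty children per group is not the number that d=0.5, 80% power and 5% alpha require: a two-sided t-test has 77.5% power at 60 and needs 64

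*Protocol article*

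**What the plan says.** The section on participants and sample size (protocol article) gives the whole calculation in one sentence: "This analysis determined that 60 children would be required in each group, totalling 120 children, to detect a moderate effect size difference between groups". In the same sentence the effect is put at a Cohen's d of 0.5, and the operating characteristics are given as "with 80% power and a 5% alpha level". The calculation is said to rest on "pilot testing of items in the Child Involvement Questionnaire (the primary outcome"). The paragraph states neither the test nor whether the 5% is one-sided or two-sided.

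Two other places bear on how to read it. The study design section describes two independent groups with no direction given: "comparing responses from children and parents who underwent a survey-based assessment procedure to responses from those who instead had a meeting-based assessment procedure". The data analysis plan names the tests in general terms: "The questionnaires will be analysed using inferential statistical analysis such as t-test and analysis of variance". The abstract carries the same total forward as the recruitment target: "We aim to recruit 120 children aged 7–17 diagnosed with ASD but without intellectual disability".

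**The concern.** Effect size, alpha, power and group size determine one another once the test is fixed. The effect is given as a standardised difference, so no pilot standard deviation held elsewhere can alter the answer. The pilot may justify choosing 0.5, but after that choice the sample size follows. The sentence can therefore be checked as it stands, and its figures do not agree.

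This is the only power statement in the article, and it supports the primary outcome. If the primary comparison turns out non-significant, readers will weigh that result against an 80% chance of detecting d=0.5. On the conventional reading, that chance is somewhat lower than stated.

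**Working it through.** **Inputs.** From the sample-size paragraph: n = 60 per group, equal groups, d = 0.5, power 80%, alpha 5%. From the data analysis plan: a t-test. Two-sidedness is an assumption. It is the usual convention and fits the undirected wording. The one-sided case is shown as well.

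**Step 1. Can 60 be reproduced? Normal approximation.**

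n per group = 2(z_alpha + z_power)² / d²

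- Two-sided: 2(1.960 + 0.842)² / 0.25 = 62.8, so 63 per group (126 in total).
- One-sided: 2(1.645 + 0.842)² / 0.25 = 49.5, so 50 per group.

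Neither gives 60.

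**Step 2. The same with the t distribution.** Power is the probability that a noncentral t variable with 2n − 2 degrees of freedom and noncentrality d√(n/2) falls beyond the critical value.

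- Two-sided: 80% is reached at n = 63.8, so 64 per group (128 in total). Power is 79.5% at 63 and 80.1% at 64.
- One-sided: 80% is reached at n = 50.2, so 51 per group.

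Again neither gives 60.

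**Step 3. Power at the stated 60 per group.** The noncentrality is 0.5 × √30 = 2.739, with 118 degrees of freedom.

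| Reading | Critical value | Power at 60 per group | n per group for 80% |
|---|---|---|---|
| Two-sided 5%, t-test | 1.980 | 77.5% | 64 |
| Two-sided 5%, normal approximation | 1.960 | 78.2% | 63 |
| One-sided 5%, t-test | 1.658 | 85.9% | 51 |
| One-sided 5%, normal approximation | 1.645 | 86.3% | 50 |

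**Step 4. Effect detectable with 60 per group.** Solving the two-sided t-test power for 80% at n = 60 gives d = 0.516 (0.511 by the normal approximation).

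**Step 5. Would a rank test explain it?** No. The four-point items might suggest a Mann-Whitney test. With its asymptotic efficiency of 3/π under normality, the two-sided requirement rises to 64 / 0.955 = 67.0, about 67 to 68 per group. That is further from 60.

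**The case against.** The best defence is rounding. The paragraph says the calculation drew on pilot results, and it prints the effect to one decimal. An unrounded d of about 0.516 to 0.520 requires exactly 60 per group in a two-sided t-test at 80% power, and it would be printed as 0.5. The pilot estimate is not shown, so this can be neither confirmed nor excluded. It does not make the printed sentence reproduce, but it is a good reason to attach the condition of d = 0.50 exactly to the 77.5%.

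The second defence is a one-sided test. The article says the new model is meant to increase the child's participation, so a directional hypothesis is conceivable. Power at 60 would then exceed 80%. But the article states no such test, and 60 would still not be the number required, which would be 51. One can get from 51 to 60 by allowing for 15% loss (51 / 0.85 = 60.0), but no such allowance is stated. These routes show that the derivation is not visible. They do not show that the figures agree.

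That the article is condensed is a fair answer to missing detail. It does not answer a stated result that disagrees with the inputs in its own sentence.

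A reader might go further and infer that the study has no margin for children who give no primary outcome, because the recruitment target equals the stated requirement. The document does not support making that part of this point. A loss allowance is something a condensed article may leave to the full protocol. The article gives no loss rate, so any resulting power would rest on an assumed one. It does plan multiple imputation for missing data. Nor would complete data rescue the 80%: on the two-sided reading, power is 77.5% with all 120 children analysed.

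**Conclusion.** The stated figure is wrong as written, by a small amount. For a two-sided two-sample t-test at d = 0.50 and 5% alpha, 60 per group gives 77.5% power, 2.5 points below the claim (1.8 points by the normal approximation). The shortfall equals four children per group (64 − 60), or a detectable effect of 0.516 instead of 0.50. The conclusion rests on two conditions that the article does not state: that the test is two-sided and that d is exactly 0.50. The weaker statement, that 60 is not the required number, holds for both the two-sided and the one-sided test at d = 0.50.

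It would be an over-reading to call the study materially underpowered or to say that it must recruit 128 children. A difference of 0.016 in detectable d has little practical weight, and a sample giving 77.5% power is a defensible choice if it is described as such. This is a minor numerical correction.

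**What to change.** Replace the power sentence with one that reproduces. Either of these will do:

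- State that 60 children per group give 77.5% power to detect d = 0.50 (80% power for d = 0.52), using a two-sample t-test at a two-sided 5% level.
- If the calculation used an unrounded pilot effect size or a one-sided test, state that effect size or sidedness, so that a reader can reproduce 60 from the inputs shown.

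In both cases, name the test and its sidedness. The cost is one sentence in the sample-size paragraph. The recruitment target, design and analysis do not change. With the first option, the stated power becomes slightly less favourable.

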### The needs assessments procedures

#### Survey-based needs assessment

In the survey-based assessment, families are given comprehensive information about the CYHC along with questionnaires which are to be completed and then returned for assessment by a team of professionals. The child is provided with a questionnaire designed to explore areas of daily challenges and areas where assistance is needed, covering topics such as sleep patterns, stress levels, worries, personal hygiene and time management skills. Additionally, the child is asked if they would like more information about their autism diagnosis. Parents are provided with a comprehensive questionnaire that delves into various aspects of their child’s well-being, including sleep patterns, stress levels, worries, eating habits, personal hygiene, time management skills, social interaction and communication abilities. Additionally, parents are given the opportunity to express whether they require further information regarding autism diagnosis or assistance from family and community support networks and to identify the two most pressing areas for intervention.

Based on the responses on the questionnaires and information from the child’s medical record, the team of professionals prioritise and recommend initial treatment options and place the child on a waiting list for the appropriate specialist.

#### Meeting-based needs assessment

In the meeting-based assessment, families are provided with comprehensive information about the CYHC and then contacted to schedule four meetings. These meetings take place at the CYHC and involve the child, one parent and a healthcare professional such as an occupational therapist or a special needs educator. Depending on the child’s age and the arrangements made, the parent may participate throughout the entire meeting or during specific segments.

The purpose of the first meeting is to establish a connection with the therapist, to create an alliance and to allow the child to acclimate to the new environment, understand the diagnosis, feel heard and leave with a positive experience. The second meeting delves deeper into the child’s experience and preferences for meetings, necessary adaptations and activities. In the third meeting, the therapist provides insight into autism and its impact on brain function and then engages the child in discussion about their experience of stress and of maintaining energy balance over time. In line with these discussions, the therapist may also suggest activities aimed at promoting overall well-being. The fourth meeting focuses on summarising the child’s autism profile, identifying their needs and prioritising treatments based on appropriateness rather than simply availability of professionals. Each meeting typically lasts between 30 and 45 min.

### Data collection and instruments

Patients will be invited to participate consecutively as they are diagnosed and registered at the CYHC. Data will be collected using questionnaires, interviews and texts from the children’s IHPs. Figure 1 summarises how and to whom the questionnaires will be distributed. The questionnaires will appear in different variants to suit the two cohorts as well as the person answering (child, parent or health professional). Questionnaires will be compiled in a booklet to make it easier to fill them in. The inclusion of patients is planned to begin in June 2024, and the expected completion of the study is December 2025.

**Figure 1 F1:**
[figure not shown]
Flowchart of the project process. ASD, autism spectrum disorder; CYHC, Child and Youth Habilitation Centres; MHC-SF, Mental Health Continuum-Short Form.

#### Measures

*Background questions*. A set of eight sociodemographic questions concerning the child and the family.

*Your child’s strengths, abilities and special needs*. This questionnaire, adapted from the Family Outcome Survey,^14^ aims to gather insights into parents’ understanding of their child’s profile. Parents respond on a 5-point Likert scale ranging from ‘Nothing/Never’ to ‘Everything/Always’. Two versions are available: one with four questions for use before needs assessment meetings and another with five questions for use after the final meeting or for the survey-based group after the needs assessment completion. This questionnaire is completed solely by parents.

*Perceived collaboration with the neuropsychiatric team*. Comprising five questions, this questionnaire assesses the family’s interaction with the neuropsychiatric team at the CYHC and the child’s involvement during these interactions. Responses are provided on a 5-point Likert scale. This questionnaire is completed solely by parents.

*The Mental Health Continuum-Short Form(MHC-SF)*.^15^ This questionnaire consists of 14 questions rated on a 6-point Likert scale, measuring mental health across three domains: emotional, psychological and social well-being. The MHC-SF has been validated from 7 years of age in Portuguese speaking children^16^ and from 12 years of age in Swedish speaking children.^17^ In the present project, three versions are available: one where the child self-reports, one where the parent self-reports and one where the parent assesses the child’s mental health (proxy assessment).

*Cantril ladder*.^18^ This tool evaluates QoL using a visual representation of a ladder numbered from 0 (lowest QoL) to 10 (highest QoL) in a valid and reliable manner.^19^ It is completed solely by the children.

*The child’s involvement*. This questionnaire contains seven to nine questions regarding participation and engagement during needs assessment meetings. It is available in three versions: one for the child, one for the parent and one for the healthcare professional. Each version has two variants tailored for regular meetings and the closing meeting. Responses are rated on a 4-point Likert scale ranging from ‘Not at all’ to ‘Very much’.

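### As worded, the Measures text gives parents in the survey-based cohort no baseline on the parent-knowledge outcome, so post scores could not be adjusted for initial knowledge and change could not be compared between cohorts

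*Protocol article*

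**What the plan says.** The abstract lists "the parents’ knowledge of their child’s strengths, abilities and special needs" among the secondary outcomes and does not define it as a change. Under Measures, the parent questionnaire adapted from the Family Outcome Survey has two versions: "one with four questions for use before needs assessment meetings and another with five questions for use after the final meeting". The sentence brings in the other cohort only at this second version, with the words "or for the survey-based group after the needs assessment completion". On response format, "Parents respond on a 5-point Likert scale ranging from ‘Nothing/Never’ to ‘Everything/Always". No rule is given for combining items, and the overlap between the two versions is not stated.

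The section on the present study also asks whether "the new needs assessment model will lead to the parent changing their view on their child’s ability to act".

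Under Data collection and instruments, "Figure 1 summarises how and to whom the questionnaires will be distributed", and "The questionnaires will appear in different variants to suit the two cohorts as well as the person answering". Families are invited one after another as the child is diagnosed and registered at the centre. For analysis, "The questionnaires will be analysed using inferential statistical analysis such as t-test and analysis of variance", with correlation and multiple regression for associations and multiple imputation for missing data. The study is described as observational and non-randomised, with 60 children planned per cohort.

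**The concern.** A before form makes sense only if the authors want to know where parents started. The sentence describing it ties that form to meetings and brings in the survey-based group only when it reaches the after form. If data collection follows the sentence, the meeting-based cohort has a pre and a post measurement and the survey-based cohort has a post measurement alone.

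Two things would be lost. Parents in the two cohorts may differ in initial knowledge, because nothing was randomised. Without a baseline in one cohort, that difference cannot be taken out of the post comparison. Secondly, any rise in the meeting-based cohort has no counterpart to set against it, so an effect of the model cannot be separated from the passage of time or from answering the form twice.

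This cannot be left to the analysis stage. A variable that was never collected in a whole cohort cannot be credibly imputed, because the data hold no information on its distribution in that cohort.

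**Working it through.** The plan states no figure for this outcome, so there is none to reproduce. The check sets the text side by side.

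**Who gets which form, as worded**

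| | Four-item form (before) | Five-item form (after) |
|---|---|---|
| Meeting-based cohort | yes, before the meetings | yes, after the last meeting |
| Survey-based cohort | not mentioned | yes, once the assessment is complete |

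**Does the before form reach the survey cohort by another route?** The description of the survey-based procedure contains no meetings: families return questionnaires, a team assesses them, and the child joins a waiting list. The meeting-based procedure has four meetings. So the condition attached to the four-item form is met in one cohort only. No sentence says that survey parents complete a baseline form, and none says that they do not.

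**What can be estimated under that schedule?**

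- Difference in post score between cohorts: yes, on the same five-item form.
- The same difference adjusted for initial knowledge: no, because the covariate is absent in one cohort.
- Difference in change between cohorts: no, because change does not exist in one cohort.

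**How much could the missing adjustment matter?** Let D be the initial difference in knowledge between cohorts in SD units, and r the pre-post correlation, with equal SDs on both occasions. The unadjusted post difference equals the model effect plus r × D. The documents give neither D nor r, so these values are assumptions. With D = 0.5 (the size that the plan calls moderate for its primary outcome):

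- r = 0.3: 0.3 × 0.5 = 0.15 SD
- r = 0.5: 0.5 × 0.5 = 0.25 SD
- r = 0.7: 0.7 × 0.5 = 0.35 SD

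With D = 0 the bias is zero. The point is that D could not be examined.

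**Secondary gain in precision.** With the baseline as covariate, the residual variance is 1 − r² of the post-only variance: 0.91, 0.75 and 0.51 for r = 0.3, 0.5 and 0.7. If one parent per child answers, 60 per group would then be worth roughly 60/0.91 = 66, 60/0.75 = 80 and 60/0.51 = 118 per group in a post-only comparison. This assumes cohorts balanced at baseline; imbalance reduces the gain.

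**Unequal item counts.** Four against five items is not in itself a barrier. Using only the items that appear in both versions puts both occasions on the same scale.

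**The case against.** The strongest reply is that Figure 1 is where the article says distribution is shown, and that figure was not available to this review. It may well show survey parents completing the first form. This stands, and it is why the conclusion is limited to the wording and the fix starts with a check against the figure.

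A second reply is that the Measures section uses the word meetings loosely. The child's involvement questionnaire is also described in terms of meetings, yet it is the primary outcome and is to be compared across both cohorts. The survey group may be named at the after form only because it has no final meeting to mark the end. This is a plausible reading. It weakens the inference about what the authors intend, but it does not supply the missing statement.

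A third reply is that the abstract names knowledge and not change as the outcome, and that a post comparison on one identical form meets that definition. This also stands. The question about parents changing their view concerns the child's ability to act, and no sentence names this questionnaire as its measure. The article acknowledges limited causal inference. That acknowledgement does not make a cheap baseline covariate less useful.

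Two stronger readings are tempting. A reader might infer that the cohorts cannot be compared on this outcome at all. The shared five-item form shows otherwise. A reader might also infer that the added item builds in a false gain. If items were coded 1 to 5 and summed, a parent answering 3 throughout would move from 4 × 3 = 12 to 5 × 3 = 15. But no scoring rule is stated and nothing proposes subtracting a four-item total from a five-item total, so no effect size can be attached to this. The absent scoring rule alone would be detail that an article may leave to a fuller document.

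**Conclusion.** The concern holds as a conditional point about the text. As worded, the survey-based cohort has no baseline on a named secondary outcome. If that is the real schedule, the cohorts can be compared on post scores only, without adjustment for initial parent knowledge, and change cannot be compared between them.

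The documents do not allow the bias to be sized. Under the assumptions shown (initial difference 0.5 SD, pre-post correlation 0.3 to 0.7) it would be 0.15 to 0.35 SD, and it vanishes if the cohorts start equal. The primary outcome is not affected. The point is worth acting on because the loss, if real, cannot be repaired after data collection. If Figure 1 already gives survey parents the first form, what remains is a correction of wording.

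**What to change.** 1. Check Figure 1 and the survey cohort's booklet. If survey parents already complete the four-item form before their assessment, reword the Measures sentence so that it names both cohorts for the first form.
2. If they do not, give the four-item form to parents in both cohorts at registration, before either procedure starts. Families are already approached at that point.
3. State that cohorts are compared on the post score with the baseline score as covariate (ANCOVA). This fits within the multiple regression that the plan already names.
4. For any pre-post change, use only the items common to both versions and report any item without a counterpart separately.

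The cost is four extra questions for survey families. Survey parents already enrolled and past their assessment cannot supply a true baseline, so the date of the change should be recorded. Baseline adjustment reduces confounding by initial knowledge but does not remove other differences between the cohorts, so the article's caution on causal inference should stay.
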